## Abstract

No data is available about pharmacological secondary prevention of superficial vein thrombosis (SVT) despite 10–15% of patients develop venous thromboembolic complications at 3–6 months after an adequate treatment of the acute phase. To verify efficacy and safety of mesoglycan in secondary prevention of SVT recurrence and venous thromboembolic complications. Phase III multicenter, double-blind, randomized, superiority trial comparing mesoglycan 50 mg bid vs placebo in consecutive patients with a SVT extended at least 5 cm, after the initial 45-day treatment course with fondaparinux 2.5 mg once-daily. Primary efficacy outcome: SVT recurrence/extension, symptomatic venous thromboembolism (VTE), asymptomatic proximal deep-vein thrombosis, death. Primary safety outcome: major bleeding. We hypothesized a 12-month 15% incidence of the primary efficacy outcome in placebo group and a 50% risk reduction in mesoglycan group. A bilateral log-rank test with a sample of 650 patients (randomization 1:1) reach a 90% power, with an α-error of 0.025, of detecting a 7.0% difference (HR = 0.51) after 12 months of treatment, considering a 10% patients drop-out. At deadline (December 31, 2022) 570 patients have been randomized (10% drop rate). Mean age was 63.9 years, 58.8% were women. SVT involved great saphenous vein in 69.3%, small saphenous vein in 13.1%, and collaterals in 17.6% of patients. SVT was the first event in 61.7%, a recurrence in 38.3%, provoked in 50.2% and unprovoked in 49.8%. Patients not experiencing a primary outcome, or not retiring their consent will be followed up to December 31, 2024 when the final data analysis will be performed

ClinicalTrials.gov: NCT03428711.

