### Statistical analysis and sample size

From the available data in the literature we hypothesize a risk of the occurrence of the primary efficacy outcome in the placebo group at the end of the treatment of 15% (that is, a cumulative proportion of 85% of subjects without events) and a 50% decrease in risk in the mesoglycan group (HR = 0.5) [3, 5, 9].

A two-sided log-rank test with an overall sample size of 650 subjects (of which 325 are in the placebo reference group and 325 in the mesoglycan treatment group) achieves a power of 90%, at a significance level (alpha) of 0.025, to identify a difference of 7.2%, between 15.0 and 7.8% (the proportions of subjects with primary endpoint in the placebo and mesoglycan group, respectively) after 12 months of treatment. This corresponds to a hazard ratio (HR) = 0.50. Subjects will be enrolled in the study for 24 months, and 50% of enrollments will be completed in month 12. The calculation considers the loss of subjects enrolled during follow-up of 10.0% in the placebo group and 10.0% in the mesoglycan group. 650 subjects will be enrolled and randomized 1:1 in the two placebo and mesoglycan arms.

This number seems large enough to guarantee the study an adequate “power” (> 0.80) even if the risk of observing the primary endpoint in the placebo group (hazard rate control) is the difference in efficacy between the two treatments (hazard ratio) that will deviate significantly from those hypothesized.

However, an “interim-analysis” is prepared when 3/4 of the subjects (n = 488) are enrolled so that the “Data and Safety Monitoring Committee” can reformulate the number of subjects to be enrolled (“resampling”) to reach the preset study power (90%) if the number of primary endpoint events observed up to then deviates significantly from the expected for the two groups, i.e., if the HR differs from the estimated one (50%) exceeded 5% in absolute value (a lower deviation seems tolerable based on the above simulation).

The alpha error is, therefore, conservatively set at 0.025 (O'Brien-Fleming method).

For the interim analysis, a tabular description of the frequency of the primary efficacy endpoint will be provided to the Committee, stratified by treatment group but without its label (i.e., without identifying the nature of the treatment assigned to each group).

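### Enrolment ended at 570 of 650 planned patients, but the only power stated is the 90% for 650, a figure the 12-month inputs do not support

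*Protocol article*

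**What the plan says.** All references are to the protocol article.

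- **Planned size.** Under Statistical analysis and sample size: "A two-sided log-rank test with an overall sample size of 650 subjects" "achieves a power of 90%, at a significance level (alpha) of 0.025, to identify a difference of 7.2" percentage points, "between 15.0 and 7.8% (the proportions of subjects with primary endpoint in the placebo and mesoglycan group, respectively) after 12 months of treatment". The text adds "This corresponds to a hazard ratio (HR) = 0.50" and allows for 10% loss in each arm. It concludes that "650 subjects will be enrolled and randomized 1:1 in the two placebo and mesoglycan arms".
- **Changing the size.** An interim look is planned once 488 patients are enrolled, at which the monitoring committee "can reformulate the number of subjects to be enrolled" so as to preserve 90% power. No outcome of that step is reported.
- **Adequacy.** The same section calls power above 0.80 adequate. That remark is made about 650.
- **Achieved size.** In the Abstract: "At deadline (December 31, 2022) 570 patients have been randomized (10% drop rate"). The Abstract then describes only follow-up to the end of 2024 and the final analysis.
- **Outcome window.** Under Study outcomes, the primary efficacy outcome is the first event during the treatment period, which is 12 months.
- **Effect size in the Abstract.** The Abstract gives the target differently: "of detecting a 7.0% difference (HR = 0.51) after 12 months of treatment, considering a 10% patients drop-out".

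**The concern.** Both 650 and 570 count randomised patients, so they compare like for like: 650 − 570 = 80, and 80/650 = 12.3%. The article states a target with its power and reports that enrolment closed below the target. It leaves the power statement as it was. A reader of the final result, above all of a non-significant one, would then weigh it against a 90% that belongs to a sample that was not enrolled.

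A second issue appears once the power for 570 is worked out. Scaling down the printed 90% is only safe if 90% is right for 650, so that figure has to be checked too.

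**Working it through.** **Inputs** (Statistical analysis and sample size, Study outcomes, Abstract): N = 650 planned and 570 achieved; 12-month event proportions 0.150 and 0.078; hazard ratio 0.50; two-sided alpha 0.025 (z = 2.2414); power 90% (z = 1.2816); 10% loss per arm. Assumptions: constant hazards, and the 10% loss read as loss over the 12 months.

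**Step 1: hazard ratio.** ln(0.922)/ln(0.850) = 0.500, so 15.0% against 7.8% does correspond to a hazard ratio of 0.50.

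**Step 2: can the printed 90% at 650 be reproduced?** Schoenfeld's formula for 1:1 allocation requires

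d = 4 (2.2414 + 1.2816)² / (ln 0.50)² = 103.3, so 104 events.

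Expected events in the 12-month window with 325 per arm:

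- no loss: 325 × (0.150 + 0.078) = 74.1
- 10% exponential loss: the observed proportion in each arm is λ/(λ+η) × (1 − e^−(λ+η)), with λ = −ln(1 − p) and η = −ln 0.9. This gives 0.1426 and 0.0741, and 325 × 0.2167 = 70.4.

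Power = Φ(√d/2 × |ln 0.50| − 2.2414):

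- 74.1 events: Φ(2.983 − 2.241) = 77.1%
- 70.4 events: Φ(2.908 − 2.241) = 74.8%

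The 90% is not reproduced.

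**Step 3: power at 570, accepting the printed 90%.** (2.2414 + 1.2816) × √(570/650) − 2.2414 = 1.058, and Φ(1.058) = 85.5%. The loss is 4.5 points.

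**Step 4: power at 570 from the 12-month inputs.** With 285 per arm, events are 285 × 0.228 = 65.0 without loss and 285 × 0.2167 = 61.7 with loss.

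| Randomised | Loss | Events | Power, alpha 0.025 |
|---|---|---|---|
| 650 | none | 74.1 | 77.1% |
| 650 | 10% | 70.4 | 74.8% |
| 570 | none | 65.0 | 71.0% |
| 570 | 10% | 61.7 | 68.5% |

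The drop from 650 to 570 is 6.1 to 6.3 points.

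**Step 5: sensitivity to the formula.** Freedman's version replaces √d/2 × |ln HR| by √d × (1 − HR)/(1 + HR) = √d/3. It gives 73.5% and 71.1% at 650, and 67.2% and 64.7% at 570. The levels are lower, and the drop is again about 6 points.

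**Step 6: detectable effect.** Solving the Schoenfeld power formula for the hazard ratio, with placebo at 15% and the event count recomputed for each ratio, 570 patients give 90% power at a hazard ratio of about 0.39 to 0.41 and 80% at about 0.45 to 0.46. For comparison, 650 patients need about 0.42 to 0.43 for 90%. Most of the distance from 0.50 is therefore present before any shortfall.

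**The case against.** The strongest reply is that nothing is hidden and little is lost. The 570 appears in the sentence right after the power statement, and the Methods section is a prospective sizing. On the article's own 90%, the achieved power of 85.5% still exceeds the 0.80 it calls adequate. The first two statements stand. The third depends on the 90%, which Step 2 does not reproduce; from the 12-month inputs, neither 650 nor 570 reaches 80% at alpha 0.025.

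It may also be said that the sizing counted events beyond 12 months. With 24-month accrual plus 12 months, or 24 months per patient, and 10% yearly loss, 650 gives about 92 to 95% and 570 about 87.5 to 92%. But the article ties the primary outcome to the treatment period and the power to 12 months of treatment, so that reading conflicts with its own text.

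Some stronger readings are tempting but not supported:

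- **That the closure breached the plan.** The article also foresees a 24-month enrolment period, and the outcome of the step at 488 is not shown. Whether the committee or an amendment set 570 cannot be told from this document.
- **That only 513 of the 570 count.** Setting 513 (570 less 10%) against 650 would deduct loss on one side only, because the 90% already allows for it. Against 585 (650 less 10%) the ratio is unchanged and the answer is again 85.5%.
- **That losses will exceed the allowance.** The 10% drop rate is undefined, and neither its timing nor the actual accrual pattern is given, so no projection is warranted.

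**Conclusion.** The point holds as a statement of power that was not updated. The trial closed enrolment at 570, and the document gives power only for 650. The shortfall costs about 4.5 points on the printed 90%, or about 6 points when power is worked from the 12-month inputs. It does not by itself explain a power of 69 to 71% at 570: on the same basis 650 gives only 75 to 77%, and the rest of the gap to 90% is a separate error in the original sizing.

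A reader might infer that the article claims a size it does not have. It does not, because the 570 is printed beside the 650. The levels rest on constant hazards, a 12-month outcome window, 10% loss read as loss over those 12 months, and two-sided alpha 0.025. At two-sided 0.05, the default under Statistical considerations, 570 gives about 78 to 80% and 650 about 83 to 85%.

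**What to change.** 1. Keep 650 and its power as the planned sizing, labelled as such, after correcting the power against the 12-month inputs. Reconcile the two versions of the effect (7.2 points with hazard ratio 0.50 in the Methods, 7.0 points with 0.51 in the Abstract) at the same time.
2. Beside it, in the Abstract and under Statistical analysis and sample size, state the achieved size (570), the expected 12-month events (about 62 to 65 on the stated inputs), the power for 15.0% against 7.8% at the alpha actually used, and the hazard ratios detectable with 80% and 90% power.
3. State that enrolment closed by date, and whether the planned re-estimation at 488 took place and changed the target.
4. In the final report, interpret a non-significant result against the achieved power, not 90%.

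The cost is wording and a short recalculation, which can be done before the final analysis. No trial procedure changes, but the stated power falls.

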## Highlights

Superficial vein thrombosis is frequently associated to venous thromboembolismNo data is available about secondary prevention of superficial vein thrombosisMesoglycan could prevent recurrences with a long-term treatment versus placeboLacking data on the natural history of the superficial vein thrombosis will be recorded

## Introduction

Superficial vein thrombosis (SVT) is a relatively common clinical condition characterized by a combination of thrombosis, inflammation, and pain along the course of a superficial vein [1]. A recent epidemiological community study clearly showed an incidence of SVT of 0.64% per year, which is six times higher than the incidence of venous thromboembolism (VTE), with an annual diagnosis rate ranging from 0.04 [95% CI, 0.00–0.10%] in men aged 18–39 years to 2.2% [95% CI,1.59–2.78%] in women aged > 75 years [2].

Considered a benign disease for a long time, SVT was recently shown to be associated with deep vein thrombosis (DVT) and symptomatic pulmonary embolism (PE) in up to 25% and 13% of cases, respectively [2, 9]. Proximal SVT (thigh) was also found to be associated with asymptomatic PE in up to 33% of cases [2, 9].

Patients with SVT and obesity, cancer, male sex, personal or family history of VTE, or severe chronic venous insufficiency are at increased risk of developing short- and long-term complications of VTE [10–14].

Indeed, recognizing a strong association between SVT and VTE in the last 10–15 years significantly modified the perceived risk of the former and its therapeutic approach, especially in the acute phase. In this respect, only fondaparinux (2.5 mg OD for 45 days) was shown to significantly reduce VTE complications, SVT extension, or recurrence by approximately 80% compared to placebo; while studies with low molecular weight heparins gave conflicting or less conclusive results [9, 10, 15, 16]. Consequently, fondaparinux (2.5 mg OD for 45 days) currently represents the first choice for the acute phase treatment of patients with SVT of the lower extremities [17].

Once completed the treatment of the acute phase, several studies have shown the utility of a treatment extension, either with vitamin K antagonists, or with direct oral anticoagulants, or low-molecular-weight heparins, or even aspirin or sulodexide as compared to no treatment in preventing VTE recurrence in patients with a first DVT and/or PE event [18–22].

On the contrary, no data is available on the need for extended treatment / secondary prevention of thromboembolism after SVT. However, despite adequate anticoagulant treatment in the acute phase, the incidence of VTE complications is as high as 15% at 3–6 months from the index event [3, 5, 15].

Mesoglycan is a complex mucopolysaccharide formed by a blend of natural glycosaminoglycans, mainly heparin-sulfate and dermatan-sulfate. Pharmacokinetic animal studies (in rats and monkeys) with tritium-labeled mesoglycan showed peak plasma levels of mesoglycan between 30 and 120 min after oral administration [23, 24]. The steady-state condition was maintained for up to 7 h; presumably due to a slow-release of the drug, after absorption by the gut-wall [23, 24]. To the contrary, peak plasma levels were recorded almost instantaneously after intravenous administration, with a subsequent rapid concentration fall within 60 min, following a biphasic course [23, 24].

The pharmacological activity of mesoglycan is expressed at the endothelial and subendothelial level, and is mainly due to the presence of heparan and dermatan sulfate, which are physiological constituents of the vessel wall.

Concerning its pharmacological effects, mesoglycan is a mild thrombin inhibitor with complementary action mediated by antithrombin and heparin-cofactor II, and is also profibrinolytic, stimulating the tissue plasminogen activator. It also exerts an antiatherogenic effect, via the inhibition of platelet adhesion, the stimulation of enzyme lipoprotein lipase, and the inhibition of the proliferation of smooth muscle cells of the tunica media; and an antiinflammatory effect via reduction of plasmatic concentration of several different cytokynes (such as MMP2, MMP9, IL6, TNFα, ICAM1, VCAM1) [25–31]. Furthermore, limited to the venous side of the circulatory system, mesoglycan is able to restore the physiological properties of the selective barrier represented by capillary endothelium, restoring flow-mediated vasodilation in subjects with endothelial dysfunction, repairing venous wall damage caused by chronic venous insufficiency, and accelerating the healing of venous ulcers [25–28]. Mesoglycan does not significantly influence coagulation parameters. In the literature there is only a small study showing a statistically significant decrease in fibrinogen plasma concentrations and an improvement in erythrocytes filterability following mesoglycan treatment, but no effect was found on prothrombin time, activated partial thromboplastin time or antithrombin levels [32].

While the efficacy of mesoglycan in preventing recurrence after a (first) episode of DVT is documented, there is no published evidence on the efficacy and safety of mesoglycan for the prevention of recurrence in patients with SVT of the lower limbs [33, 34].

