### Study population and randomization

Subjects of both sexes, > 18 years of age, with objectively documented SVT of the lower limbs, initially extended for at least 5 cm, who had completed the standard 45-day course with fondaparinux 2.5 mg OD, were asked to participate in the study. Patients could only be included if they consented to participate within two weeks from treatment withdrawal. The complete list of inclusion and exclusion criteria is reported in Table 1.

**Table 1 Tab1:** Inclusion and exclusion criteria for METRO study

Inclusion criteria	Exclusion criteria
Age ≥ 18 years Objective diagnosis of SVT of the lower limbs documented with Color Coded Doppler Ultrasound of at least 5 cm extension, not involving the last 3 cm of the great saphenous vein and of the small saphenous vein, close to the respective sapheno-femoral and sapheno-popliteal junction Completion of the initial treatment of the acute phase with fondaparinux 2.5 mg once daily for 45 days With a negative ultrasound scan for SVT recurrence/extension and/or DVT at the end of the acute phase treatment. treatment	Little adherence to the treatment of the acute phase with Fondaparinux or its premature withdrawal before the deadline of 45 days Interval between the end of fondaparinux treatment and recruitment > 15 days Mandatory anticoagulation for other clinical diseases than SVT Life expectancy < 24 months Scarce compliance or impossibility of filling or answering the questionnaires Pregnancy or breastfeeding Severe muscoloskeletal disability or prolonged immobilization Concomitant participation in another clinical trial or previous participation in the last 3 months Overt post-thrombotic syndrome with a Villalta Score > 4 Chronic lymphedema of the lower limbs Recent (< 3 months) or planned surgery for varicose veins or PTA angioplasty Dyalisis Malabsorption or malnutrition Chronic use of high doses of phlebotonics, steroids, or nonsteroidal anti-inflammatory drugs, mandatory dual antiplatelet therapy or aspirin > 160 mg once daily, central painkillers Known hypersensitivity to mesoglycan or heparin or heparinoids Intolerance to galactose or lactase enzyme deficiency Bleeding tendency

After signing the informed consent, eligible subjects will complete the screening visit. Only patients who meet the inclusion and exclusion criteria will be included.

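### The 15% placebo risk is not shown to apply to patients who are event-free after fondaparinux, and the assurance that power stays above 0.80 under departures from the assumptions is wrong

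*Protocol article*

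**What the plan says.** Two places give a background risk, with different starting points. In the Introduction, "the incidence of VTE complications is as high as 15% at 3–6 months from the index event". In the Abstract, "10–15% of patients develop venous thromboembolic complications at 3–6 months after an adequate treatment of the acute phase".

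The planning value is set in Statistical analysis and sample size: "we hypothesize a risk of the occurrence of the primary efficacy outcome in the placebo group at the end of the treatment of 15" per cent, with a hazard ratio of 0.50. The Abstract gives the horizon: "We hypothesized a 12-month 15% incidence of the primary efficacy outcome in placebo group and a 50% risk reduction in mesoglycan group".

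Table 1 defines who can be randomised. It requires "Completion of the initial treatment of the acute phase with fondaparinux 2.5 mg once daily for 45 days" and "With a negative ultrasound scan for SVT recurrence/extension and/or DVT at the end of the acute phase treatment", and it excludes patients with "Interval between the end of fondaparinux treatment and recruitment > 15 days".

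Under Study outcomes, the primary composite adds symptomatic SVT recurrence or extension and death to the VTE events, and counts first events during the treatment period only.

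The sample-size section claims 90% power for 650 patients. It then says that this number keeps power above 0.80 even under significant deviation. That sentence is garbled; I read it as covering both the control hazard and the hazard ratio. The Abstract reports that recruitment closed with 570 randomised.

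**The concern.** The two background statements differ in time origin by at least the 45-day fondaparinux course. If the clock starts at the index event, the figure includes early events that would keep a patient out of the trial. If it starts after acute treatment, it does not. The sample-size section does not say which basis its 15% has, nor that it is a risk from randomisation in event-free patients.

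Event count, and so power, depends on the control risk in patients who can actually be randomised. A reader who cannot tell whether 15% fits this population has only the robustness statement to rely on. If that statement is wrong, an inconclusive result from 570 patients would be read against a power that the trial did not have.

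**Working it through.** **Inputs from the protocol.** Control risk 15.0% and mesoglycan risk 7.8% at 12 months; two-sided alpha 0.025 (z = 2.241); power 90% (z = 1.282); 650 patients, 1:1; 10% loss per arm; endpoint limited to 12 months of treatment. Randomised: 570.

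**The plan's own figures.**
- HR = ln(0.922)/ln(0.85) = 0.4997, so the stated 0.50 reproduces.
- Events needed (Schoenfeld) = 4(2.241 + 1.282)²/(ln 0.5)² = 103.3, so 104.
- Yearly hazards: control λ = −ln 0.85 = 0.1625; mesoglycan 0.0813; loss δ = −ln 0.90 = 0.1054.
- Proportion with an observed event = λ/(λ+δ) × [1 − exp(−(λ+δ))] = 0.1426 and 0.0741.
- Events with 650 patients = 325 × (0.1426 + 0.0741) = 70.4.
- Power = Φ(0.693 × √70.4/2 − 2.241) = Φ(0.667) = 75%.

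The stated 90% does not reproduce. With no losses at all, events are 325 × (0.15 + 0.078) = 74 and power is 77%. About 90% returns only if events after month 12 are counted up to a common close at roughly month 30–33, which conflicts with the treatment-period endpoint.

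**Departures from the assumptions, same method.**

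| Placebo risk, 12 months | HR | Events 650/570 | Power 650/570 |
|---|---|---|---|
| 20% | 0.50 | 94/83 | 87%/82% |
| 15% (planned) | 0.50 | 70/62 | 75%/68.5% |
| 10% | 0.50 | 47/41 | 55%/49% |
| 8% | 0.50 | 37/33 | 45%/40% |
| 15% | 0.60 | 75/66 | 49%/43% |

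With HR 0.50, power above 0.80 needs a placebo risk of about 17% with 650 patients and a little over 19% with 570.

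**A more generous reading.** Suppose later events were counted, with 24 months of uniform accrual and a common close at month 36. With 650 patients, power is 95% at 15% risk and 83% at 10%. It falls to 73% at 8%, and to 76% at 15% risk with HR 0.60. With 570, the 10% row gives 77%.

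**Which way eligibility and horizon move the risk.** Suppose a share f of a 15% index-event risk falls before randomisation (f is my assumption; the documents give none). The remaining risk among event-free patients is 0.15(1 − f)/(1 − 0.15f): 11.7% for f = 0.25 and 8.1% for f = 0.50. These are risks over the rest of the 3–6 month window, not over 12 months. In the other direction, a constant hazard of 15% per six months gives 1 − 0.85^(365/182) = 27.8% over the year after day 45. A declining hazard would give less. The wider composite raises the risk further.

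**The case against.** A reader might infer that 15% is known to be too high because eligibility removes early events, and that the trial is therefore underpowered. The documents do not support this, for four reasons.

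- The Abstract's clock starts after acute treatment, which is close to the trial's own population. Nothing settles which clock is right.
- The Introduction's figure and the planning figure are different quantities: VTE complications at 3–6 months against a wider composite at 12 months. They share a number and two of three citations, but the sample-size section does not say that one is the other.
- The share of events before randomisation has no source in the documents.
- The exclusions do not all point one way in effect. Patients with cancer or prior DVT/PE remain admissible, since both are candidate covariates in the primary analysis, and the Introduction names cancer and a history of VTE as raising risk.

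It is also fair to say that a journal article may leave the derivation of 15% to the full protocol. The planned re-estimation at 488 enrolled is a partial safeguard against a wrong control risk. However, its trigger ends as a deviation of the HR from 50%, and recruitment closed below 650.

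These points defeat the claim that 15% is wrong. They do not rescue the robustness statement, which fails whatever the source of the 15%. Nor should the drop from 90% to 75% be blamed on eligibility: it arises at the protocol's own 15%, from limiting the endpoint to 12 months.

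**Conclusion.** The point holds in a limited form. The time origin of the background risk is stated inconsistently, and 15% is not shown to be the 12-month composite risk of patients event-free after fondaparinux. Its direction of error, if any, is open.

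The assurance of power above 0.80 under significant deviation is incorrect. On the treatment-period endpoint it is not met even at the planned values (75% with 650 patients, 68.5% with 570). At 10% risk power is about half, and at HR 0.60 it is below half. It holds only if the placebo risk is clearly above plan or the effect is larger than HR 0.50. Counting events to month 36 does not save it for HR 0.60 or for an 8% risk.

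These figures assume exponential event and loss times, proportional hazards, 12 months at risk per patient and Schoenfeld's approximation. Freedman's formula gives slightly lower power (69–74% against 72–77% at the planned values with 650 patients, across ways of handling loss).

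**What to change.** 1. Use one time origin for the background risk in the Abstract and the Introduction.
2. In Statistical analysis and sample size, state the 12-month composite placebo risk assumed from randomisation in patients event-free after fondaparinux, and its basis.
3. Restate the design power for the 570 randomised over a placebo risk of about 8–20%, including the 15% row, with the follow-up horizon made explicit.
4. Delete the statement that power stays above 0.80 under significant deviation, and adjust the later remark that relies on the same simulation to call small HR deviations tolerable.

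The cost is wording and a short recalculation. Enrolment is unchanged. The downside is a less favourable stated power, which should be given as a planning quantity and not computed from the observed results.
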